### Sample size

The sample-size calculation is based on change in RDQ at three months after onset of LBP. It is recommended that a change in 2 to 3 points on the RDQ should be considered the minimum clinically important change [22]. To allow for the cluster randomisation by PHCC, we assume an intraclass correlation coefficient of 0.1 [34] and a minimum average number of individuals sampled per PHCC of 25. In order to detect a difference of 2.5 points between the two intervention arms with a standard deviation of 5.7 [22,35], an alpha error of 0.05, a beta error of 0.10, and a 20% dropout rate, a sample size of 932 subjects was required, 466 subjects per intervention arm. Therefore, the total number of PHCCs is 38 (19 for group).

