### Statistical Analysis

Data will be analysed in accordance with CONSORT guidelines, extension to cluster randomised trial. Data will be analysed by intention-to-treat. To address potential biases due to incomplete follow-up, we will analyse patients with complete data at all time points and those with data at any time point, using the last known value carried forward to replace missing values. Bias due to non-response will be assessed at each follow-up.

The primary end points for the trial will be 3 months (short term), 6 months and 12 months (long term).

We will obtain descriptive statistics for the outcome measures, baseline characteristics and clinical measures as mean (standard deviation) or numbers (percentages), with 95% confidence intervals at each assessment for all the patients and for each group.

The distribution of data will be checked to ensure that parametric assumptions are met, and non-parametric analyses will be used when appropriate. We will use independent *t *tests or Mann-Whitney U tests for continuous data and Χ^2 ^tests or Fisher's exact probability test for categorical data for unadjusted comparisons between groups at each assessment.

Continuous data for change in scores from baseline will be compared between groups and for each group. The paired t-test for difference will be used to compare the change between pre- and post- intervention.

To decide on an important change in individuals, we will contrast the distributions of changes in all the questionnaires and in each assessment, in individuals who change to chronic state and in individuals who do not [22]. We will do the same between those individuals who return to work and those who do not. We will compare individual change scores to the standard error of measurement (SEM).

To detect changes in groups, the intervention effect will be calculated through the effect-size for each questionnaire and at each assessment. Effect-size was calculated following the method of Kazis et al [36]

We will evaluate responsiveness of each scale by standardised response mean (SRM) [37] and receiver-operating characteristic method (ROC curve). The SRM will be performed between two-time points (baseline and each assessment) and for each intervention arm. We have chosen recovery according to the patient as an external criterion for clinically relevant improvement.

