Simple correlations between the scores of the different scales (disability, severity of pain, quality of life and psychosocial scales) will be obtained through the Pearson linear correlation coefficient or the Spearman correlation, in the case of parametric assumptions not being met, at each assessment.

Since the unit of randomisation is the PHCC, we will use a regression analysis of individual level data using methods for clustered data [38]. For adjusting comparisons and to account for cluster randomisation, multilevel linear regression analyses on repeated measures on each of the outcome scales will be used to assess the effect of intervention and to investigate the factors that influence each of the outcome scales at each time point adjusting for baseline scores, baseline characteristics of patients (socio-demographic, clinical and professional) and the other scale scores if they are found to affect outcomes significantly over time. The possible association between intervention and time will be studied. The PHCC and the individual will be considered as random effects and intervention and time as fixed effects.

A multilevel Cox regression model will be used to evaluate the association between the main independent variable, the prognostic factors and the time of subsiding of the current episode of LBP or return to work at 3 months. The patients for whom the duration of the current episode is more than 3 months or those who do not return to work at 3 months will be censored at that time. Kaplan-Meier survival curves will be used to compare the rate of evolution to chronicity and return to work between both groups. Logrank and Breslow test will be used for testing the equality of survival among groups.

The differences in medication prescription at baseline and at each assessment in the interventions and control groups will be compared.

We will calculate the relative risk reduction (RRR) and number needed to treat (NNT) to facilitate development of clinical guidelines for future management.

We will study the interactions and the collinearity. The collinearity of the maximal models will be evaluated using the criteria proposed by Belsley [39]. The significance level of all models will be set at 5%.

The SPSS statistical package for Windows, version 17 (SPSS Inc., Chicago, IL) and the SAS 9.1.3 for Windows (SAS Institute Inc., Cary, NC, USA), will be used for statistical analysis.

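### The random effects named for the repeated-measures model have no PHCC-by-time term, so the intervention-by-time test would not allow for cluster randomisation if centre effects vary between visits

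*Protocol article*

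**What the plan says.** The Statistical Analysis section adjusts for clustering in this way: "multilevel linear regression analyses on repeated measures on each of the outcome scales will be used to assess the effect of intervention". Baseline scores enter as covariates. The random and fixed parts are then named: "The PHCC and the individual will be considered as random effects and intervention and time as fixed effects". The section adds: "The possible association between intervention and time will be studied". On error rates it says: "The significance level of all models will be set at 5" per cent. On timing it says: "The primary end points for the trial will be 3 months (short term), 6 months and 12 months (long term").

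The Sample size section supplies the clustering figures: "we assume an intraclass correlation coefficient of 0.1 [34] and a minimum average number of individuals sampled per PHCC of 25", with 19 PHCCs per arm. It gives one ICC. The article does not say how stable centre effects are from one visit to the next, and it gives no within-patient correlation.

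**The concern.** Intervention arm is a property of the centre. Whether the arm difference changes between visits is a within-patient contrast, so a constant centre effect and a constant patient effect both cancel out of it. If those are the only two random terms, the error left for testing the interaction is the pooled patient-level residual, on about 1,500 degrees of freedom. Any change in a centre's deviation between visits enters the arm-by-time contrast in full but barely enters its standard error. The model then allows for clustering in the average arm effect but not in how that effect changes over time.

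The plan separates short-term from long-term results and applies the model to every outcome scale. A liberal interaction test could lead the trial to report a benefit that fades or grows when only the centres have drifted. An arm contrast at a single visit read from the same model would also have an interval that is a little too narrow.

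**Working it through.** **The plan's own figure.** The target is stated as: "detect a difference of 2.5 points between the two intervention arms with a standard deviation of 5.7", with "an alpha error of 0.05, a beta error of 0.10, and a 20% dropout rate". Taking alpha as two-sided:

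- Per arm before inflation: (1.960 + 1.282)² × 2 × 5.7² / 2.5² = 109.2.
- Design effect: 1 + (25 − 1) × 0.1 = 3.4.
- 109.2 × 3.4 / 0.8 = 464 per arm, or 468 if 109.2 is first rounded up to 110. The protocol states 466, so the sample size is not in question.

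**Inputs for the interaction test.**

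- From the protocol: K = 38 PHCCs, ICC ρ = 0.1, m = 25 × 0.8 = 20 analysed per PHCC, and T = 3 post-baseline visits (baseline is a covariate). The SD of 5.7 cancels, so total variance is set to 1.
- Assumed: the ICC of 0.1 applies at every visit.
- Assumed: r, the correlation of a PHCC's effect between visits, from 1.0 to 0.5.
- Assumed: w, the share of within-PHCC variance that persists in a patient across visits, 0.4 and 0.6.

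**Formulas**, for balanced data with constant PHCC and patient effects fitted:

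- Centre-by-time variance: v_ct = ρ(1 − r).
- Residual variance: v_e = (1 − ρ)(1 − w).
- True error variance of the arm-by-time mean square: v_e + m·v_ct.
- Error variance the model uses: v_e + f·v_ct, where f = 20 × 36 × 2 / 1,516 = 0.95. Here 1,516 = (760 − 2) × 2 is the residual degrees of freedom.
- V is the true error variance divided by the one used. Rejection rate of the 2-df test ≈ exp(−2.996/V), which is 5% at V = 1.

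Example, r = 0.9 and w = 0.4: v_ct = 0.01 and v_e = 0.54. V = (0.54 + 0.20)/(0.54 + 0.0095) = 1.347, and exp(−2.996/1.347) = 10.8%.

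**3-month contrast.** The true variance of a PHCC mean at one visit is 0.1 + 0.9/20 = 0.145. The model implies ρr + v_ct/3 + [0.9 + f·v_ct × 2/3]/20. At r = 0.5 this is 0.05 + 0.0167 + 0.9317/20 = 0.1132. The ratio is 1.28, and P(|Z| > 1.96/√1.28) = 8.3%. This does not depend on w.

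| r | Interaction, w = 0.4 | Interaction, w = 0.6 | 3-month contrast |
|---|---|---|---|
| 1.0 | 5.0% | 5.0% | 5.0% |
| 0.95 | 7.8% | 9.3% | 5.3% |
| 0.9 | 10.8% | 13.9% | 5.5% |
| 0.8 | 16.8% | 22.4% | 6.1% |
| 0.5 | 31.9% | 40.8% | 8.3% |

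Simulation with 6,000 trials per setting agrees to within about 1.5 percentage points; its highest value at r = 0.5 was 42.2%. If 25 patients per PHCC are analysed and baseline is treated as a fourth outcome visit, the single-visit figure at r = 0.5 rises to 9.3%.

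**With the PHCC-by-time mean square as the error term** (2 and 72 degrees of freedom), simulated rejection stays between about 4.3% and 5.9% at every r tried.

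**Scale.** At r = 0.9 the centre-by-visit SD is √(0.01 × 5.7²) = 0.57 points on the 0-24 RDQ.

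**The case against.** The strongest reply is that the article does not say intercepts only. It names PHCC and individual as random effects and is silent on slopes, residual covariance, standard errors and degrees of freedom. A condensed article may leave these to a fuller plan. That stands as a limit: the point rests on a plain reading of the named terms. It does not remove the point, because the article does state the random part, and that part has no centre-by-time term.

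The second reply is about size. A reader might infer that the planned test rejects a true null several times too often as a matter of fact. The documents do not support that. They give no between-visit centre correlation; there is no inflation at 1.0 and less than a doubling at 0.95, and the largest figures need half of the between-centre variance to be specific to a visit. Some features limit drift: the same patients are followed, one psychologist and one physiotherapist serve all centres, and both arms are assumed to follow the same guideline. Others leave room for it: the GP and nurse delivering sessions are not standardised in that way, and the Discussion allows that usual practice may vary. Neither set fixes a value.

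Third, the interaction is a supporting analysis with no decision rule attached, and the sample size rests on RDQ change at 3 months. This stands. Calling 3, 6 and 12 months all primary concerns the arm contrasts at those visits, not the interaction.

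**Conclusion.** The point holds in conditional form. As named, the random effects do not protect the intervention-by-time test against centre effects that vary between visits, and nothing in the protocol supports taking those effects as identical at 3, 6 and 12 months. Over the assumed range (within-patient correlation about 0.4 to 0.6), the type I error at a nominal 5% is about 5% at a between-visit PHCC correlation of 1.0, 7-9% at 0.95, 11-14% at 0.9, 17-23% at 0.8 and 32-42% at 0.5.

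A reader might go further and infer that the main 3-month comparison is invalid. It is not: its error rate is about 5-6% at 0.9 and reaches about 9% only at the far end of the range. The change is worth making because it is cheap, but the trial's main comparison does not depend on it.

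**What to change.** Add a PHCC-by-time random effect to the multilevel linear model. Test intervention-by-time, and the arm contrasts at 3, 6 and 12 months, with denominator degrees of freedom based on the number of PHCCs, for example Kenward-Roger in SAS, which the plan already names. The added term gives an exchangeable centre-level structure with two variance parameters. An unstructured PHCC covariance over three visits has six; it is a richer alternative, not an equivalent.

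The cost is one sentence in the analysis section and one extra term in the code, with no new data or patients. Intervals widen where centre-by-time variance is present. For the interaction, the standard error grows by √V: about 16-23% at a correlation of 0.9 and 62-83% at 0.5. For a single-visit contrast the increase is about 2% at 0.9 (√1.046) and 13% at 0.5 (√1.28). If the added variance is estimated as zero, the random structure reduces to the stated one.

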### Study population

Eligible patients will be consecutively selected by their GP, who will inform them about the study objectives. All patients who agree to participate will be given written informed consent to sign.

Patients will be included if the current episode of LBP occurs suddenly after a period of a minimum of 6 months without LBP and lasts between 15 days and 12 weeks [15] and if they do not fulfill any of the exclusion criteria [3].

Furthermore, patients have to be between 18 and 65 years old, and understand Catalan or Spanish and will be accessible for at least twelve months.

Patients will be excluded if: they are unwilling to participate in the multidisciplinary intervention trial; LBP coexists with cognitive impairment or severe psychiatric disorders such as psychosis, or if they have severe major depression; any other cause of disability which impedes answering the various questionnaires; they are pregnant or breast-feeding; they might have anti-inflammatory intolerance or allergy; treatment for physical problems in the preceding three months has been given; and they have been referred for intensive functional restoration programmes or if they have a confirmed diagnosis of fibromyalgia.

Furthermore, the GP has to ensure that the patient has no red flag signs or symptoms that are frequently associated with specific LBP or potentially severe illnesses [5,16,17].

Red flags for possible specific spinal pathology are: oncologic disease during the previous 5 years; constitutional symptoms, unexplained weight loss, fever, chills, recent urinary tract infection; history of drug or alcohol abuse, or immunocompromised host; vertebral fracture (previous history of major trauma: traffic accidents or falls from heights: patients with risk factors of osteoporosis, long term treatment with glucocorticoids); inflammatory spondylarthropathy (SpA) (pain of typical inflammatory night-pattern pain which forces the patient to get up from bed, gradual onset of pain before the age of 40, severe morning stiffness, limited low back mobility on the sagittal/lateral plane, possible inflammatory involvement of peripheral joints, family history, extra-articular manifestations: uveitis, iritis, psoriasis, colitis, urethritis).

Red flags for surgical referral: saddle anaesthesia, recent onset of bladder dysfunction or anal sphincter impairment, major or progressive motor weakness, sensory level, or widespread neurological signs.

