### Other non-pharmacological therapeutic measures and Patient Compliance

During the intervention period, other non-pharmacological therapeutic measures which differ from those stated in the intervention design will be advised against. However, in the case of non-pharmacological therapeutic measures occurring, they will be registered and included in the analysis.

In the follow-up visits at 3, 6 and 12 months, we will ask about the patient compliance of recommendations of treatment and the questionnaires will be completed. Furthermore, if the patient is unable to attend the follow-up visits, the data collection will be carried out by telephone call.

Compliance to the group sessions will be assessed by registering the number of group sessions that patients attend.

To ensure patients' adherence to the group sessions, they will be asked a time preference (morning or afternoon) to attend the sessions. One week prior to the group session, they will receive a phone call to report the date, time and location of the session and on the day before, an SMS message with the same information will be sent.

At the end of the study, the control group will receive the compact disc of Jacobson's progressive relaxation technique, the educational booklet "The Back Manual" and the audiovisual.

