- *Quality of Life measured by SF-12*. We will use the Spanish version of SF-12 because for large group studies, the differences in measurement reliability between the SF-12 and SF-36 are not as important and the SF-12 is worthwhile for specific populations based on large sample sizes [28]. The 12 items provide a representative sampling of the content of the 8 health concepts and operational definitions of those concepts, including what respondents are able to do, how they feel, and how they evaluate their health status. The dimensions were physical function (2 items), physical role (2), social functioning (1), emotional health (2), mental health (2), vitality (1), bodily pain (1), general health (1). The answer options on the Likert scale evaluate the intensity and frequency of these dimensions. Time reference in the version used is 4 weeks. Scores rate from 0 for worse health status to 100 for best health status, for each of the dimensions. The questionnaire should preferably be self-administered.

Secondary outcomes are:

- *Duration of the current episode of LBP (pre-study and study duration)*. We will consider the current episode finished when the pain and its impact on the person's daily life is reduced, even when the pain cannot be cured completely [29].

- *Work sick leave (yes or no)*

- *Duration in days of work sick leave*

- *Percentage of change in pharmacological treatments*.

- *Wrong beliefs, inadequate behaviour and work factors assessed by Fear Avoidance Beliefs Questionnaire (FAB) *[30]. Among psychosocial factors associated with LBP, avoidance behaviour of physical activity or work due to fear of pain have been demonstrated to have an influence on the disability. The Spanish version of the FAB questionnaire allows us to quantify beliefs and fears regarding the causes and consequences of pain, with validity and accuracy in patients with LBP. This questionnaire, recently validated, contains 16 statements (five related to physical activity and eleven to work activity), which patients score from 0 to 6 depending on their degree of agreement or disagreement. Thus, higher scores indicate a higher degree of avoidance behaviour. Completion takes around ten minutes and it can be self-administered.

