**Figure 1 F1:**
[figure not shown]
**Study flow chart**. Notes: PHCC = Primary Health Care Centres; GP = General practitioner.

**Table 4 T4:** Overview of data collection

	*Baseline*	*Follow-up*		
**Outcome Measures**	**15 days after onset of LBP**	**3 months**	**6 months**	**12 months**

Disability: Roland Morris Questionnaire (RDQ)	X	X	X	X

McGill Pain Questionnaire	X	X	X	X

Quality of life Questionnaire (SF-12v2)	X	X	X	X

Duration of the current episode LBP	X	X	X	X

Work sick leave (yes or no)	X	X	X	X

Duration of work sick leave in days	X	X	X	X

Percentage of change in pharmacological treatments	X	X	X	X

Fear Avoidance Beliefs Questionnaire (FAB)	X	X		X

Goldberg Scale (Anxiety and Depression) Questionnaire	X	X		X

Satisfaction with care	X	X	X	X

Patients' perceived global assessment	X	X	X	X

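### Each time-to-event outcome gets a log-rank test, a Breslow test and a Cox model with no main test named, and the two plain tests ignore centre clustering

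*Protocol article*

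**What the plan says.** The Statistical Analysis section of the protocol article gives three analyses for the same two time-to-event outcomes.

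- Curves: "Kaplan-Meier survival curves will be used to compare the rate of evolution to chronicity and return to work between both groups".
- Tests on those curves: "Logrank and Breslow test will be used for testing the equality of survival among groups".
- Model: "A multilevel Cox regression model will be used to evaluate the association between the main independent variable, the prognostic factors and the time of subsiding", or return to work, at 3 months. Patients still in the episode are censored at 3 months, as are "those who do not return to work at 3 months will be censored at that time".

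No test is named as the main one. The section sets 5% for all models and gives no separate level for the tests.

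Four other places bear on the point. The Outcomes section lists episode duration and sick leave as secondary and counts the pre-study part of the episode, so its clock starts at onset. Under Study population, an eligible episode "lasts between 15 days and 12 weeks", while the data collection table (Table 4) puts baseline at "15 days after onset of LBP". On session timing, the section on patient compliance says only this: "One week prior to the group session, they will receive a phone call". Intervention Design gives the intervention arm a booklet in addition to the group sessions, with groups of up to 12.

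**The concern.** Two tests and a model answer one question, and nothing fixed in advance says which answer counts. If they disagree, the choice can follow the results.

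The two plain tests also treat patients as independent, although centres were randomised. The sample size section itself assumes an intraclass correlation of 0.1 for the disability score, so the authors expect clustering to matter.

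The two tests also weight time differently. Breslow weights each event time by the number still at risk, so it leans on earlier events than log-rank does. If benefit begins only once the group sessions have been held, the early events carry no effect and Breslow is the weaker test.

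At stake are the claims about shorter episodes, less progression to chronic pain and earlier return to work. The primary result on the Roland Morris score is not affected.

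**Working it through.** **The plan's own figure.** The article gives no event count, hazard ratio or power for the time-to-event outcomes. Its only sample size is for the disability score:

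- n per arm = 2 × (1.960 + 1.282)² × 5.7² / 2.5² = 109.2
- design effect = 1 + (25 − 1) × 0.1 = 3.4; 109.2 × 3.4 = 371.4
- 20% dropout: 371.4 / 0.8 = 464.3 per arm (468 if 109.2 is first rounded up to 110), against 466 stated
- centres: 932 / 25 = 37.3, so 38

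This reproduces. It supplies the inputs below but does not itself test the point.

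**Simulation inputs.**

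- From the article: 932 × 0.8 = 746 patients, 38 centres, clock from onset, censoring at day 90 (3 months), and entry either all at day 15 (Table 4) or spread evenly over days 15 to 84 (the eligibility window).
- Assumed: a constant recovery hazard of −ln(p)/75 per day after entry, where p is the share unresolved 75 days after entry (day 90 for entry at day 15). p = 0.37 gives 0.0133 and p = 0.10 gives 0.0307. The two values borrow the Background's 37% still in pain at two months and the Discussion's upper figure of 10% becoming chronic or recurring.
- Assumed: a hazard ratio of 1.35 that starts 7, 14 or 28 days after entry. The article does not state this lag.
- Power runs ignore clustering and use 1,000 trials each.

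**False positives, no true effect.**

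| Between-centre SD of log hazard | Log-rank | Breslow | Either |
|---|---|---|---|
| 0 (10,000 trials) | 0.049-0.051 | 0.049-0.050 | 0.061-0.070 |
| 0.3 (3,000 trials) | 0.17-0.20 | 0.16-0.18 | 0.19-0.23 |
| 0.5 (3,000 trials) | 0.30-0.33 | 0.29-0.31 | 0.32-0.37 |

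Ranges span p = 0.37 and p = 0.10. A second null simulation without clustering gave 5.4% to 6.6% for either test. Two independent tests would give 1 − 0.95² = 9.75%. The real figure is lower because the two tests are strongly correlated. Most of the excess comes from ignoring PHCC, and the second test adds a little.

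**Power, log-rank / Breslow.**

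| Entry and risk sets | p | 7-day lag | 14-day lag | 28-day lag |
|---|---|---|---|---|
| All at day 15 | 0.37 | 0.83 / 0.73 | 0.71 / 0.56 | 0.44 / 0.26 |
| All at day 15 | 0.10 | 0.88 / 0.61 | 0.68 / 0.30 | 0.30 / 0.09 |
| Spread, no delayed entry | 0.37 | 0.52 / 0.49 | 0.36 / 0.31 | 0.15 / 0.13 |
| Spread, no delayed entry | 0.10 | 0.51 / 0.43 | 0.29 / 0.24 | 0.08 / 0.06 |
| Spread, delayed entry | 0.37 | 0.55 / 0.55 | 0.30 / 0.33 | 0.13 / 0.15 |
| Spread, delayed entry | 0.10 | 0.66 / 0.67 | 0.36 / 0.40 | 0.11 / 0.13 |

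Breslow loses in every row without delayed entry, heavily when all enter at day 15. With spread entry and delayed-entry risk sets it is level or slightly ahead.

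**Where the weight falls.** Days 0 to 15 carry 0% in every scenario, since no event occurs then. With all entering at day 15, the share between entry and session is 19-35%, 34-58% and 59-83% for Breslow at lags of 7, 14 and 28 days. For log-rank it is 13-21%, 25-39% and 47-64%.

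**The case against.** The strongest defence is that the cluster-adjusted analysis is already there. The section commits to methods for clustered data and plans a multilevel Cox model for these outcomes. On that view the log-rank and Breslow tests merely accompany the Kaplan-Meier curves, and two weightings show when the curves part. The outcomes are secondary, and the extra error from the second test is one or two percentage points. This limits the weight of the point but does not remove it. The text assigns the two tests to testing equality of survival, does not call them descriptive, and does not say that the Cox result prevails.

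A reader might infer three stronger things, and the article supports none of them.

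- That Breslow puts most of its weight on the first days after onset. For episode duration this cannot be so, because an eligible episode has lasted at least 15 days. For return to work the time origin is not stated, so nothing firm can be said there.
- That no effect is possible before a known session date. The wait is not given, only a reminder call a week ahead. The intervention arm also receives a booklet at an unstated time, so an arm difference before the sessions cannot be ruled out.
- That Breslow is the weaker test whatever the time origin. With spread entry and delayed-entry risk sets it is not.

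**Conclusion.** The point holds in a limited form. The plan names three analyses for each time-to-event outcome and no main one, and two of the three ignore PHCC. That much rests on the text alone.

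The error from being free to choose either plain test is about 6-7% without clustering. The larger figures, 16-33% for a single plain test, rest on an assumed between-centre SD of 0.3 to 0.5, for which the article gives no value on these outcomes.

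The power loss from Breslow is conditional. It needs a clock from onset without delayed-entry handling and an effect that starts only after the sessions. Its size then depends on the session lag, the spread of entry times and the recovery rate, none of which is given. The power figures ignore clustering and assume a hazard ratio of 1.35, so they compare the two tests and do not forecast this trial's power. They also use all 746 patients, whereas return to work concerns only those on sick leave.

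This is a minor specification point on secondary outcomes.

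**What to change.** State that, for the end of the episode and for return to work, the single between-arm test is the arm term of the multilevel Cox model already planned, at the 5% level. A log-rank test in a form that allows for PHCC would serve equally well. Drop the Breslow test, or report it beside the Kaplan-Meier curves as descriptive only. Stating the time origin and the handling of delayed entry in the same sentence would settle the conditional part of the point.

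The cost is a sentence or two in the analysis section, with no new data and no new model. The one real loss is some sensitivity to early differences between arms, for example from the booklet. A descriptive Breslow statistic would still show these.
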